**Methods:**

This single-arm trial will include 20 patients undergoing unilateral transfemoral or transtibial amputations. HAL-assisted gait training will be performed 5 days per week (30 minutes per session) until postoperative week 8. The primary outcome is a 2-minute walking distance, while secondary outcomes include muscle strength, balance, gait parameters, and ADL/QOL measures. Statistical analyses will be conducted using SPSS (IBM Corp), and results obtained at the following time points will be compared: preoperative, postintervention, and 6-month follow-up.

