**Results:**

The planned sample size is 20 patients, calculated using JMP version 12 (SAS Institute) based on an expected 1.5-fold improvement in 6-minute walk distance (effect size 0.8, α=.05, power=0.8). Analyses will be performed using SPSS version 15.0 (IBM Corp). The 2-minute walk test (primary outcome) and secondary outcomes will be compared at baseline, post intervention, and 6-month follow-up using 1-way analysis of variance or Kruskal-Wallis test, and *P* values <.05 and 95% CIs will be reported.

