### Statistical Analysis

The target sample size was set at 20 patients scheduled for lower limb amputation. Using JMP version 12 (SAS Institute), the sample size was calculated based on a research design assuming that the 6MWD would improve by a factor of 1.5, referencing previous studies on gait analysis using the HAL [16]. The calculation was performed with α=.05, power=0.80, and a prespecified effect size.

The primary analysis population for efficacy evaluation will be the Full Analysis Set (FAS), whereas the secondary analysis population will be the Per Protocol Set (PPS).

The FAS includes all study participants who have undergone at least one session of HAL-assisted gait training and have had at least one efficacy-related observation thereafter. However, individuals who fail to meet the eligibility criteria will be excluded. The PPS comprises participants from the FAS who have completed HAL-assisted gait training (5 days per week, 30 minutes per day) without major deviations from the study protocol and for whom the primary evaluation item can be assessed.

Statistical analyses will be conducted using SPSS version 30.0 (IBM Corp). The primary evaluation item, the 2-minute walking distance, will be analyzed using the FAS population, and the mean (SD) [or median (minimum-maximum)] will be calculated. Comparisons between preoperative, postintervention, and 6-month postoperative outcomes will be performed using a 1-way ANOVA or the Kruskal-Wallis test, with a 2-sided significance level of 5%, and a 95% CI will be calculated. In addition, the same analysis will be performed using the PPS as a secondary approach.

For secondary evaluation items, analysis will also be conducted using the FAS population. The mean (SD) [or median (minimum-maximum)] will be calculated for bilateral lower limb muscle strength, skeletal muscle mass, sensory impairment, range of motion, Berg Balance Scale, timed up and go test, gait parameters (step length, stride length, weight distribution, and gait speed during the 10-minute walk test), maximal oxygen uptake, and Locomo 25. Comparisons between preoperative, postintervention, and 6-month postoperative outcomes will be performed using a 1-way ANOVA or the Kruskal-Wallis test, and multiple comparisons will be conducted using the Tukey method (or Steel-Dwass test). A 2-sided significance level of 5% and a 95% CI will be used. The same analysis will also be performed using the PPS as a secondary approach.

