Furthermore, for Barthel Index (BI), Functional Independence Measure (FIM), Frenchay Activities Index (FAI), SF-36, Health Utilities Index, EQ-5D-5L (quality-adjusted life years), long-term care insurance certification level, General Self-Efficacy Scale, and WHODAS 2.0, the mean (SD) [or median (IQR)] will be calculated. Comparisons between preoperative, postintervention, and 6-month postoperative outcomes will be performed using a 1-way ANOVA or the Kruskal-Wallis test, with multiple comparisons conducted using the Tukey method (or Steel-Dwass test). A 2-sided significance level of 5% and a 95% CI will be calculated. The same analysis will be conducted using the PPS as a secondary approach.

The primary efficacy analysis will be conducted using the FAS, which includes all participants who received at least one session of HAL-assisted gait training and have at least one postintervention efficacy observation. Participants who are found to violate key eligibility criteria will be excluded from the FAS.

A secondary analysis will be performed using the PPS, which is a subset of the FAS consisting of participants who completed HAL training (5 days per week, 30 minutes per session) without any major protocol deviations and for whom the primary outcome data are available.

For missing data, a descriptive analysis will first be conducted to assess the pattern and mechanism of missingness. If the data are judged to be missing at random, multiple imputation using chained equations will be applied to handle missing values in the primary outcomes. Additionally, sensitivity analyses will be performed by comparing results between complete-case and imputed datasets to evaluate the robustness of the findings.

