### Planned Outcomes and Statistical Analysis

For the primary outcome, the 2MWD, we will compare results at 3 time points: preoperative, post intervention, and 6-month follow-up. Data will be presented as mean (SD) [or median (minimum-maximum)]. Comparisons will be performed using a 1-way ANOVA or the Kruskal-Wallis test, with a *P* value <.05 and 95% CIs reported.

Secondary outcomes will be analyzed using a similar approach. Descriptive statistics will be calculated for objective measures, like muscle strength, balance, and gait parameters, as well as for subjective scales including ADL/QOL assessments (BI, FIM, and FAI). Multiple comparisons will be conducted using the Tukey method or the Steel-Dwass test, with a *P* value <.05 and 95% CIs also reported.

For missing data, we will first conduct a descriptive analysis to assess the pattern of missingness. If the data are judged to be missing at random, multiple imputation will be applied to the primary outcomes. Sensitivity analyses will also be performed by comparing results from complete-case and imputed datasets to assess the robustness of the findings.

The primary efficacy analysis will be conducted on the FAS, and a secondary analysis on the PPS.

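### The same 20 patients are compared at three visits with tests for independent groups, so P values and any CI for change ignore within-patient correlation

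*Protocol article*

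**What the plan says.** The abstract sets out the design: "This single-arm trial will include 20 patients undergoing unilateral transfemoral or transtibial amputations". There is no comparison group. The factor tested is time within patient; under Planned Outcomes and Statistical Analysis, for the 2-minute walk distance, "we will compare results at 3 time points: preoperative, post intervention, and 6-month follow-up".

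The named tests are:
- **Primary outcome.** Statistical Analysis: "Comparisons between preoperative, postintervention, and 6-month postoperative outcomes will be performed using a 1-way ANOVA or the Kruskal-Wallis test". Planned Outcomes and Statistical Analysis repeats this ("Comparisons will be performed using a 1-way ANOVA or the Kruskal-Wallis test"), as does the abstract ("using 1-way analysis of variance or Kruskal-Wallis test").
- **Physical-function secondary outcomes.** The same tests, and "multiple comparisons will be conducted using the Tukey method (or Steel-Dwass test").
- **ADL and QOL secondary outcomes.** The same tests, "with multiple comparisons conducted using the Tukey method (or Steel-Dwass test"). The later summary says "Secondary outcomes will be analyzed using a similar approach".

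The level is two-sided 5% with a 95% CI, and the quantity the interval estimates is not named. The per-protocol analyses repeat the same methods. Nowhere does the article mention a paired test, repeated-measures ANOVA, Friedman, Wilcoxon signed-rank, a mixed model or a patient effect.

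**The concern.** One-way ANOVA, Kruskal-Wallis, Tukey and Steel-Dwass assume that the groups contain different, independent people. Here the three groups are the same people at three times. The tests keep stable differences between patients (age, amputation level, fitness) in the error term, although these differences cancel when each patient is compared with himself or herself.

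The primary test therefore does not run at its stated 5% level. With the positive correlation usual between repeated measurements of one person, it is too cautious: P values are too large, intervals for change too wide, and real change is more easily missed. That matters with only 20 patients, and the same methods are named for the secondary outcomes and for both analysis sets.

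**Working it through.** **Inputs from the article.** n=20 in one arm; three times; two-sided 5%; sample size based on α=.05, power 0.8 and effect size 0.8. The effect size is not defined as paired or between-patient, and the test behind the sample size is not named.

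**Assumption.** The within-patient correlation ρ is not given, so it is varied. Unless stated, data are normal with equal variances and the same ρ between every pair of visits (compound symmetry).

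**Step 1. The plan's own figure.** N=20 cannot be tied to one test. At effect size 0.8 and 80% power:
- A two-sided paired t-test needs 15. Allowing an assumed 25% dropout, 15/(1−0.25)=20.
- A two-sided two-sample t-test needs 26 per group.
- A three-group 1-way ANOVA with f=0.8 reaches 80% at 19 observations in total (21 if balanced).

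So 20 can be reached on more than one reading. It neither confirms nor refutes a within-patient design, and the point does not depend on it.

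**Step 2. Why the test is off.** With common variance σ² and no true change, the expected between-visit mean square is σ²(1−ρ), while the within-visit mean square that 1-way ANOVA divides by has expectation about σ². The F ratio therefore runs at about (1−ρ) times its proper size: 0.7, 0.5 and 0.3 times at ρ = 0.3, 0.5 and 0.7. Repeated-measures ANOVA divides by a term of expectation σ²(1−ρ), so the factor cancels.

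**Step 3. Width of a CI for change.** The independent-groups interval uses standard error σ√(2/n) on 57 df; the paired interval uses σ√(2(1−ρ)/n) on 19 df. The ratio is (2.002/2.093)/√(1−ρ) = 0.957/√(1−ρ):
- ρ=0.3: 0.957/0.837 = 1.14
- ρ=0.5: 0.957/0.707 = 1.35
- ρ=0.7: 0.957/0.548 = 1.75
- ρ=0.8: 0.957/0.447 = 2.14

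**Step 4. Type I error and power by simulation** (at least 20,000 trials per setting; both follow-up visits shifted equally). A paired effect of 0.8 corresponds to a raw shift of 0.8√(2(1−ρ)) SD: 0.95, 0.80, 0.62 and 0.51 SD at the four values of ρ.

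| ρ | Type I error, 1-way ANOVA | Power at paired 0.8: 1-way / repeated-measures | Power at 0.8 between-patient SD: 1-way / repeated-measures |
|---|---|---|---|
| 0.3 | about 1.5% | 89% / 95% | 74% / 86% |
| 0.5 | 0.4% | 75% / 95% | 75% / 95% |
| 0.7 | 0.05% | 40% / 95% | 78% / nearly 100% |
| 0.8 | near 0 | 15% / 95% | 79-80% / nearly 100% |

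Repeated-measures ANOVA held its type I error at about 5% throughout this table. The rank tests behave alike: at the paired 0.8, Kruskal-Wallis against Friedman gives 71% against 86% at ρ=0.5, and 38% against 87% at ρ=0.7.

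**Step 5. Negative correlation.** Suppose preoperative walking correlates at −0.3 with each follow-up, and the two follow-ups correlate at +0.5 or +0.7. The type I error of 1-way ANOVA is then about 6-7%. Uncorrected repeated-measures ANOVA also gives about 6-7% there, because correlations differ between pairs of visits.

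**The case against.** **Loose wording.** The name 1-way ANOVA could be shorthand for one-way repeated-measures ANOVA. That defence fails for the stated alternatives: Kruskal-Wallis and Steel-Dwass are defined for independent samples, and the within-patient counterpart of Kruskal-Wallis would be Friedman. The choice also recurs in the abstract, Methods and Results.

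**Left to an unseen analysis plan.** An article may omit detail, but this one names the tests. A fuller plan that follows it inherits the problem; one that departs from it contradicts it.

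**Exploratory study, conservative error.** This stands in part. The article calls the study exploratory, and under positive correlation the risk is a missed effect. But it still commits to a 5% test and hopes the results will support wider insurance coverage.

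Stronger readings that a reader might infer, and that the documents do not support:
- **Tukey and Steel-Dwass also govern the primary outcome.** They are named only for secondary outcomes.
- **Every CI is wrong.** The article does not say what its CI estimates. One for the mean at a single visit is unaffected.
- **Most of the power is always lost.** That happens only at correlations of about 0.7 or more, and only if 0.8 is a paired effect. In between-patient SD units, 1-way ANOVA stays at about 74-80%.
- **The test seriously inflates false positives.** A rate of 10% requires −0.3 between all pairs of visits, including the two follow-ups, which is implausible.

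**Conclusion.** The point holds. The article fixes independent-groups tests for a comparison within one cohort, for the primary outcome and for the secondary outcomes. P values, and any CI for change built on these tests, are wrong unless within-patient correlation is about zero. With positive correlation the result is an over-cautious test and an interval for change 1.14 to 2.14 times the paired width over correlations 0.3 to 0.8. The power loss runs from modest (89% against 95%) to severe (15% against 95%) if 0.8 is a paired change held at month 6. Otherwise power sits at or just below the 80% target while a within-patient test reaches 86% to nearly 100%. A negative link between preoperative and later walking would make the test only slightly liberal.

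The direction follows from the design. The sizes rest on assumed correlations, normal data and, for the main table, compound symmetry. This should be corrected before analysis, as a matter of lost power and precision; it does not show that N=20 is wrong.

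**What to change.** Change the wording in the abstract, Statistical Analysis, and Planned Outcomes and Statistical Analysis:

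- **Primary.** Name the preoperative versus week-8 contrast in 2-minute walk distance, with a 95% CI for the change. The Outcomes and Limitations sections already place the primary assessment at week 8. Estimate it from a mixed model for repeated measures (visit as fixed effect, patient as subject, unstructured covariance) or by a paired t-test, and fix one of these in advance.
- **Month 6 and secondary outcomes.** Use paired contrasts from the same model with Holm adjustment.
- **Nonparametric fallback.** Use Friedman with Holm-adjusted Wilcoxon signed-rank tests in place of Kruskal-Wallis and Steel-Dwass.

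The unstructured covariance matters: with unequal variances or correlations, uncorrected repeated-measures ANOVA had a type I error of 6.6-7.9% in the simulations. It would also help to state whether the 0.8 is a paired effect and which test gave N=20.

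Cost: wording and slightly more analysis work. No extra patients or data.

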**Inclusion criteria**
Patients scheduled to undergo unilateral transfemoral or transtibial amputation at our hospital (underlying disease is not specified)Patients capable of providing written informed consentPatients aged ≥16 years at the time of consent acquisitionPatients with a height between 150 and 175 cmPatients with a body weight between 40 and 100 kgPatients deemed by a physician to have the potential to walk postoperatively with a prosthetic limbPatients able to comply with the hospitalization and treatment schedule during the treatment period

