**Physical function**			
	2-minute walking distance	Measures the total distance walked in 2 minutes, with pylons placed at 30-m intervals.	
	Bilateral lower limb muscle strength	Measured using μ-Tas (ANIMA Corporation) under isometric contraction conditions.	
	Skeletal muscle mass	Measured using InBody S10.	
	Sensory	Evaluated using a tactile sensory testing device.	
	Range of motion	Assessed using the Tokyo University–style goniometer.	
	Berg Balance Scale	Evaluates balance ability using a validated assessment form.	
	Short Physical Performance Battery	A useful measure combining balance ability and walking performance, assessed using a standard evaluation form.	
	Gait analysis	Measures time to complete the TUG and 10-m walk. Gait pattern is analyzed during the 10-m walk using the PhysiGait (CREACT Co, Ltd) gait analysis system, evaluating step length, stride length, weight distribution, gait speed, etc.	
	Cardiopulmonary function	Maximal oxygen consumption (VO₂ max): Measured using a respiratory gas analyzer.	
	Locomo 25	A questionnaire consisting of 25 items regarding body pain and difficulties in daily activities over the past month. Responses are scored on a 5-point scale (0-4 points per item). Locomotive Syndrome Grade 1: Total score ≥7 points. Locomotive Syndrome Grade 2: Total score ≥16 points.	
	Muscle activity	Electromyography (EMG): Measures muscle activity distribution patterns using a multichannel surface EMG system.	
Activity			BI (Barthel Index), FIM (Functional Independence Measure), FAI (Frenchay Activities Index).
Participation			SF-36, Health Utilities Index, Euro-Qol-5D-5L, Long-Term Care Insurance Certification Level, General Self-Efficacy Scale, WHODAS2.0, Locomotor Capabilities Index (LCI), Prosthetic Evaluation Questionnaire Japan.

All physical function assessments (2-minute walk test) will be conducted without HAL assistance.

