In addition, patient background information, including sex, date of birth, age, hospitalization status (inpatient or outpatient), height, weight, comorbidities, past medical history, current medical history, medication status, and residual limb length, will be recorded. Vital signs, such as body temperature, blood pressure, pulse rate, and respiratory rate, will also be documented. Furthermore, blood biochemical tests, including white blood cells, red blood cells, hemoglobin, platelets, creatine kinase, albumin, and C-reactive protein, as well as physiological test results, such as electrocardiogram and spirometry, will be collected. The presence or absence of adverse events, including contact dermatitis, abrasions, muscle damage due to overload, and other adverse events, will also be recorded.

The time schedule for participant enrollment, interventions (including pre- and postoperative periods), assessments, and follow-up visits is summarized in Table 2. This table is structured in accordance with the SPIRIT (Standard Protocol Items: Recommendations for Interventional Trials) 2013 statement and outlines key time points, such as preobservation, surgery, and follow-up phases (2 weeks, 8 weeks, and 6 months postoperatively).

The SPIRIT schedule is presented in table format in the manuscript and is provided to all participants as part of the informed consent process. The schedule includes key components such as enrollment procedures, including informed consent and baseline data collection; interventions, including HAL gait training and prosthesis-based rehabilitation; outcome assessments, which consist of physical function measures, blood biochemistry, and physiological tests; and safety monitoring, including adverse event tracking throughout all phases of the study.

All assessments and interventions are scheduled to ensure consistency and patient safety throughout the clinical trial.

**Table 2 table2:** Schedule of enrollment, interventions, assessments, and visits (SPIRIT^a^-compliant).

Study period	Enrollment	Preobservation	Day 0	2 weeks postoperative	8 weeks postoperative	6 months postoperative	Withdrawal
Informed consent	✓						
Participant characteristics	✓						
Physical function^b^		✓			✓	✓	
Activities^c^		✓			✓	✓	
Participation^d^		✓			✓	✓	
Blood biochemistry^e^		✓			✓	✓	
Physiological tests^f^		✓			✓	✓	
HAL^g^ gait training^h,i^		✓^h^		✓^i^	✓^i^		
Prosthesis gait training^j^					✓^j^	✓	
Adverse event monitoring		✓	✓	✓	✓	✓	✓

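### Preoperative contrasts for muscle mass, and for operated-side strength, sensation or motion below the amputation level, mix tissue removal with recovery

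*Protocol article*

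**What the plan says.** The Statistical Analysis section names "bilateral lower limb muscle strength, skeletal muscle mass, sensory impairment, range of motion" among the secondary items and states: "Comparisons between preoperative, postintervention, and 6-month postoperative outcomes will be performed using a 1-way ANOVA or the Kruskal-Wallis test". Pairwise comparisons follow by Tukey or Steel-Dwass. The error level is given as "A 2-sided significance level of 5% and a 95% CI will be used".

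The first inclusion criterion is "Patients scheduled to undergo unilateral transfemoral or transtibial amputation at our hospital", so an amputation separates the preoperative visit from both later visits. Table 2 schedules physical function before surgery, at 8 weeks and at 6 months.

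Table 1 describes "Bilateral lower limb muscle strength" only as an isometric measurement with a named device, and skeletal muscle mass only by the name of its analyser. It gives no muscle groups, joints or sensory sites, and it does not limit muscle mass to particular body segments.

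Table 1 also places "Locomotor Capabilities Index (LCI), Prosthetic Evaluation Questionnaire Japan" in the Participation block. Table 2 ticks that block before surgery, at 8 weeks and at 6 months. The list of questionnaires to be analysed ends at WHODAS 2.0 and names neither instrument.

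**The concern.** The objective is the effect of HAL-assisted rehabilitation. For a measure that the operation itself changes, the preoperative value does not refer to the same body as the later values. The change from it is the loss of tissue plus whatever recovery has taken place, and the planned test cannot separate the two.

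Two misreadings are possible. A significant fall in muscle mass could be taken for deconditioning or a failure of training when it is the removed limb. A true improvement could be cancelled or reversed in sign by the loss. Where a site below the amputation level is on the measurement list, its postoperative value is undefined rather than missing, and the planned multiple imputation covers only the primary outcomes.

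The questionnaires raise a smaller, separate matter. Two instruments concerned with prosthetic use or locomotor capability are scheduled when no study prosthesis exists, and they are then left out of the named analyses.

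**Working it through.** **Which contrasts are affected.** Let the preoperative mean be m, the mean loss caused by the amputation L, and the mean recovery by week 8 and month 6 G8 and G6. If the removed tissue contributes nothing after surgery:

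- week 8 minus preoperative = (m − L + G8) − m = G8 − L
- month 6 minus preoperative = (m − L + G6) − m = G6 − L
- month 6 minus week 8 = (m − L + G6) − (m − L + G8) = G6 − G8

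L enters two of the three pairwise contrasts and the overall test. It cancels only in the third.

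**Which items have L > 0.** Skeletal muscle mass does, because no segment is excluded. Strength, sensation and range of motion do where the site lies below the amputation level on the operated side. They do not on the intact side, at the hip, or at the knee after transtibial amputation; those sites can be measured at all three visits.

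**How strongly L could drive the tests.** The plan states no figure to reproduce here. The documents give n = 20 and a two-sided 5% level. Everything else is an assumption:

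- L from 0 to 2 SD
- G8 = G6 = G, equal to 0, 0.5 or 0.8 SD
- correlation between visits of 0.5 or 0.8
- normal data with unit SD
- 10,000 simulated trials per setting

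The tests were the one-way ANOVA as planned, a paired t-test of week 8 against preoperative, and a paired t-test of month 6 against week 8. Each cell below gives the result at correlation 0.5 / 0.8.

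| L (SD) | G (SD) | ANOVA rejects | Paired week 8 vs preop: significant improvement | Paired: significant worsening |
|---|---|---|---|---|
| 0 | 0.8 | 74.9% / 79.3% | 92.4% / 100% | 0% / 0% |
| 0.5 | 0 | 24.3% / 15.0% | 0% / 0% | 57.6% / 92.5% |
| 0.5 | 0.8 | 5.0% / 0.9% | 24.8% / 52.2% | 0% / 0% |
| 1 | 0 | 94.7% / 97.9% | 0% / 0% | 98.7% / 100% |
| 1 | 0.8 | 1.8% / 0.1% | 0.3% / 0.0% | 12.9% / 27.3% |
| 1.5 | 0.8 | 57.3% / 57.1% | 0% / 0% | 84.2% / 99.8% |

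With no rehabilitation effect, a loss of 1 SD alone makes the tests significant nearly always. With a true gain of 0.8 SD, the same loss takes the chance of a significant improvement in the paired test from at least 92% to under 1%. The month 6 against week 8 test rejected in 4.5% to 5.3% of trials in every setting, as it should when G8 = G6. The low ANOVA rates at small net change partly reflect that a one-way ANOVA ignores pairing within patients, which is a different matter.

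**Questionnaires, place by place.** Table 1 puts both in Participation. Table 2 ticks Participation preoperatively. The Interventions section has the temporary prosthesis fitted only once the residual limb has matured. The Statistical Analysis list omits both. Only the general statement under Planned Outcomes and Statistical Analysis, that secondary outcomes are handled similarly, could bring them in. The three places do not agree.

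**The case against.** Several counter-arguments have weight.

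- Measured joints and sensory sites are not stated, and an article may leave them to the full protocol. A reader might infer that operated-side values will be entirely missing after surgery. The documents do not support that: it would hold only for sites below the amputation level, if any are measured. This stands, and for three of the four items it makes the point conditional. It does not help muscle mass.
- Strength is measured on both sides and nothing says that the sides are combined. A reader might infer that gains in the intact limb must be hidden; that does not follow. The plan equally does not say that the sides are analysed apart.
- A reader might infer that these tests show only the amputation. That is too strong: the preoperative contrasts show loss and recovery together, and the planned pairwise comparisons already include week 8 against month 6, which is free of the loss.
- A reader might infer that the two questionnaires are to be tested against a preoperative value. No analysis list names them, so the documented fault is the mismatch between the tables and the list.
- The Limitations section concedes that the lack of a control group restricts attribution, and the design is called exploratory. That concession concerns the cause of a change. It does not say that surgery alters the quantity being measured.
- HAL training ends at postoperative week 8, so the clean contrast covers only the time afterwards. This stands as a real limit on that part of the remedy.

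**Conclusion.** The point holds in limited form. For skeletal muscle mass it follows directly from the text. For strength, sensation and range of motion it holds for any operated-side site below the amputation level. In those cases the overall test and both preoperative contrasts cannot be read as effects of rehabilitation.

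The size in this trial is unknown. The simulation rests on assumed losses, gains and correlations and shows the mechanism only; the direction of the distortion does not depend on those values. The primary outcome is not touched by this point. It is worth correcting because it changes what several planned secondary tests can conclude. The questionnaire matter is an inconsistency to reconcile, not evidence of an invalid planned test.

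**What to change.** 1. Analyse strength, sensation and range of motion by side. Make the inferential pre-post comparisons those on the intact side and on the operated-side joints present at all visits: the hip for all participants, the knee for transtibial amputation only.
2. Analyse skeletal muscle mass without the amputated limb at all three visits, if segment values are available. Otherwise report preoperative muscle mass descriptively and test only week 8 against month 6, stating that this interval lies after HAL training has ended.
3. Reconcile the Locomotor Capabilities Index and the Prosthetic Evaluation Questionnaire across Table 1, Table 2 and the analysis list. Compare the prosthesis-specific items only between week 8 and month 6.
4. Add to the Limitations section that the operation itself changes some of these measures.

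The cost is analysis wording and a footnote to Table 2. There will be fewer pre-post tests on the operated side, and the week 8 to month 6 contrast does not measure change during the intervention. The retained-site comparisons remain uncontrolled, so the change removes the tissue-loss artefact and nothing more.
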